## Abstract

**Background:**

Although drug treatment strategies for rheumatoid arthritis (RA) are relatively well established, there is a paucity of evidence on the treatment in older patients. The purpose of this study is to build a registry for late-onset RA (LORA), which is expected to increase rapidly worldwide. In addition, we aim to propose optimal treatment strategies according to the patient background including frailty, thereby contributing to improving the quality of treatment and daily living in patients with RA.

**Methods/design:**

The LORIS (Late-onset Rheumatoid Arthritis Registry) Study is a prospective nation-wide multicenter observational study of patients with LORA. The inclusion criteria were patients aged ≥ 65 years at onset, meeting 2010 ACR/EULAR classification criteria for RA, and starting either any disease-modifying antirheumatic drugs (DMARDs) in a DMARD-naïve patient or the first biologic/targeted synthetic DMARDs during the study period. Enrollment was started on 11 January, 2022 and will be closed on 31 December, 2023. Patients will undergo a comprehensive baseline assessment including clinical data, medication, cognitive and physical function, psychosocial factors, and frailty. Data will be collected at baseline, Month 3, 6, 12, 18, 24, 36, and summarized descriptively. The factors associated with adverse events and achieving remission will be determined.

**Discussion:**

A multi-disciplinary panel including patients, rheumatologists, and geriatric specialists will discuss the results and build a consensus regarding the treatment goals of LORA. We expect to provide a broad range of information for evidence-based shared decision making in the treatment of LORA.

*Study registration*: Registered at the UMIN registry (UMIN000046086) on 1 January 2022.

**Supplementary Information:**

The online version contains supplementary material available at 10.1186/s41927-022-00322-7.

## Background

Rheumatoid arthritis (RA) is a typical chronic autoimmune disease, where activities of daily living (ADL) will be gradually restricted owing to joint dysfunction. Currently, it is estimated that more than 800,000 patients with RA are treated in Japan, of which the late elderly patients account for 35% [1, 2]. Conventionally, RA has been considered to most commonly occur in people in their 30 s–50 s; however, people who developed RA in their late 60 s have increased in number in recent years [3]. With the advent of super-aging society, it is plausible that the number of patients with late-onset RA (LORA) increase rapidly and the establishment of treatment strategy for LORA is an urgent issue.

Drug therapy for RA has dramatically evolved in the twenty-first century, and joint destruction can now be prevented by early initiation of thorough anti-inflammatory treatment [4, 5]. In 1999, methotrexate (MTX) was approved as a therapeutic drug for RA in Japan. In 2003, infliximab, the first biologic DMARD (bDMARD), was approved; and now, 11 different bDMARDs including biosimilars can be prescribed. In addition, starting with tofacitinib in 2013, five types of Janus kinase (JAK) inhibitors have been approved, and treatment options have become remarkably wider compared to 20 years ago.

In 2020, the Japan College of Rheumatology (JCR) updated the clinical practice guidelines for the management of RA [6]. This set of guidelines included recommendations for elderly RA based on a systematic review of drug therapy, and the use of MTX and molecular targeted agents were weakly recommended with careful safety considerations [7]. However, the quality of evidence was very low because it was based on sub-analyses of RCTs. Safety information is not always reported adequately in RCT studies [8]. Lack of an evidence-based treatment strategy for elderly patients may cause insufficient control of disease activity, leading to progression of joint destruction, decreased ADL, and increased incidence of RA-related comorbidities including secondary osteoporosis and cardiovascular events.

The elderly tends to have many comorbidities and attending physicians may become overly cautious about possible adverse events (AEs) and miss the opportunities for treatment [9, 10]. Actually, based on the analysis of Nakajima et al*.* using the National Database of Health Insurance Claims [2], the proportion of patients using MTX, the anchor drug for RA treatment, decreases with age; 73% of patients in their 50 s and 38.2% in those aged ≥ 85 years. In addition, bDMARDs are administered at 24% in the 50 s, but only at 13.7% among patients aged ≥ 85 years. Meanwhile, the oral corticosteroids are used at 37.3% in the 50 s, but as high as 52.0% at 85 years or above. However, previous studies showed inconsistent results in the association between age and AEs, thereby indicating that advanced age alone is not necessarily a significant risk factor of serious AEs in RA patients treated with DMARDs. Recently, Sugihara et al*.* has reported that age was not a significant risk factor of serious AEs after adjusting for comorbidities at baseline and mean SDAI during the observation period and concluded that T2T strategy by using MTX and bDMARDs was effective and feasible for the LORA [11]. Based on retrospective cohort data in patients with RA who started treatment with biologic / targeted synthetic b/tsDMARDs, Ochi et al. reported that safety and therapeutic effectiveness were comparable between late-onset and non-late-onset cases [12].

Frailty is a concept that reflects the limited mental and physical reserve capacities of the elderly [13, 14]. In general, the elderly require treatment tailored to their biological age, which takes into account the complications of individual patients and the comprehensive functional assessment of the body and mind, that is, the severity of frailty [9, 10]. Frailty assessment at the start of treatment may guide the attending physician’s treatment selection and play a role in prognosis prediction and improvement of patient QOL [15].

Increasing medical costs due to the growing elderly population have become a social issue. b/tsDMARDs are expensive so that some patients reluctant to start. Considering the loss of workforce and care costs due to decline of ADL, early and appropriate use of b/tsDMARDs for older patients may contribute to the improvement of the health economic aspects of the problem.

Thus, prospective observational studies are necessary to confirm the safety and effectiveness of the treatment for LORA.

The objective of this study is: (1) building a registry for LORA; (2) performing a comprehensive functional assessment (i.e., physical aspects including frailty, mental and cognitive aspects, and social aspects); (3) proposing optimal treatment strategies tailored to the patient background; and (4) contributing to quality improvement of medical treatment for RA in Japan and extension of healthy life expectancy. This study is conducted to generate evidence to update the JCR clinical practice guidelines in collaborations with the JCR and the Japan Rheumatism Friendship Association [16].

## Methods/design

### Study design

The LORIS (**L**ate-**o**nset **r**heumatoid arthr**i**tis regi**s**try) Study is a prospective, nation-wide, multicenter, observational study of patients with LORA. A total of 19 leading medical institutions of RA (10 university hospitals, two national hospitals, one municipal hospital, three private hospitals, and one clinic) were requested by the steering committee to join the study as the study centers. Additional hospitals or clinic may join the study when the representatives of any study centers recommend, and the steering committee approve them.

### Participants

Participants developing RA at 65 years or older, fulfilling the 1987 American College of Rheumatology classification criteria for RA or the 2010 ACR/EULAR criteria, and who meet one of the followings are enrolled: (1) First therapy with any csDMARD is initiated, (2) First MTX treatment is initiated, or (3) First b/tsDMARDs treatment is initiated during the study period (i.e., from January 10, 2022, to December 31, 2023).

Exclusion criteria are as follows: (1) Patients who are unable or unwilling to provide written informed consent, (2) Those who have already taken any b/tsDMARDs previously, (3) Patients with any other systemic autoimmune disorders, except for Sjogren’s disease, (4) Patients who are deemed inappropriate for enrollment by the investigators, and 5) Patients in whom more than two years have passed since the diagnosis was confirmed.

### Patient and public involvement

Two patient representatives of the Japan Rheumatism Friendship Association [16] participated in the panel meeting to determine the study protocol on December 9, 2021. They are expected to join the second panel meeting which is planned in March 2024 to discuss the study results and build a consensus of treatment goals for LORA.

### Outcomes

We have two primary outcomes for this study: the safety of the treatment and changes in QOL. Specifically, we will identify followings.Factors related to survival and cause of deathFactors related to hospitalization (malignancy, infection, cardiovascular events, fracture and pneumonia)Prevalence of requiring long-term care and their gradeChanges in QOL (EQ-5D-5L) and factors related to the decline in QOLChanges in physical function (HAQ) and factors related to decline in physical function

Secondary outcomes include the treatment effectiveness and drug retention rates of the initial DMARD. We will assess proportion of those who achieve sustained clinical remission and low disease activity, and achievement of minimally clinically important difference in physical function (HAQ) and QOL (EQ5D). Sustained remission is defined as a Disease Activity Score in 28 joints (DAS28) of < 2.6 for 6 months (short-term sustained remission) or for 24, and 36 months (long-term sustained remission).

We also examine followings.Trends in frailty and sarcopeniaChanges in physical functions other than HAQ and factors related to the decline in physical functionsChanges in cognitive function and factors related to decline in cognitive functionChanges in disease activityChanges in joint destructionChanges in Patient-reported OutcomeWhether MTX is administered, the dose and interval, if not, reasons for dose increase, decrease, or discontinuationWhether or not molecularly targeted drugs are administered, and reasons for prolonging the interval, reducing the dose, or discontinuing.GCs administration or not, dose, and reasons for dose increase or decrease or discontinuationWhether or not NSAIDs are administered.

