### Data collection and management

After providing written informed consent, patients are enrolled in the registry. Clinical assessment data including physical examination, laboratory tests, and details of medication are recorded in the electronic data capture (EDC) system at each study center. The coordinating center will manage the EDC system.

Patients are asked to complete questionnaires to capture information regarding demographics and patient-reported outcomes. Present and past medical history are collected by nurses or trained clinical research coordinators and confirmed by site investigators. Clinical assessment data will be collected at baseline, Month 3, 6, 12, 18, 24, and 36. Questionnaires and interview surveys will be conducted at baseline, Month 12, 24, and 36. Detailed information of data collection is shown in Table 1.

**Table 1 Tab1:** Parameters captured by the registry database

Category	Items
Sociodemographic data	Age, sex, education, marital status
Medical history	Onset time Current symptoms of RA compared to those in the previous year Surgery for RA, site, type Total number of medications taken Vaccination history (*Streptococcus pneumoniae*, herpes zoster)
Medication	Use/non-use of MTX, start date, dose, reason for non-use (cognitive decline, interstitial pneumonia (IP), pulmonary diseases other than IP, renal dysfunction, hepatic dysfunction, history of infection, peripheral blood test results, complication/history of malignant tumor, and HBV carrier/infection, among others) Use/non-use of other csDMARDs Use/non-use of GCs, dose, administration period, and reason for administration Use/non-use of NSAIDs Use/non-use of opioids Use/non-use of molecular targeted drugs, start date, and dose Use/non-use of osteoporosis drugs (bisphosphonates, PTH preparations, denosumab, romosozumab, vitamin D preparations, and SERM)
Symptoms	Tender joint count (28・44) Swelling joint count (28・44) Physician global assessment (VAS) Patient global assessment (VAS) Physical function (HAQ-DI) Health-related QOL (EQ-5D-5L) Depression (PHQ-2) Pain and fatigue (VAS)

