Laboratory data	Inflammation marker (CRP, MMP3, ESR) Blood cell count (White blood cell, neutrophil, total lymphocyte, red blood cell, hemoglobin, and platelet) Nutritional marker (Serum total protein, serum albumin, Hemoglobin A1c, serum total cholesterol, LDL, HDL cholesterol, TG) Infection tests (HBs antigen, HBs antibody, HBc antibody, HCV antibody, IGRA, and β-D-glucan) Autoimmune tests (rheumatoid factor, antinuclear antibody, anti-SS-A/Ro antibody, and anti-CCP antibody) Renal function (Serum creatinine, Serum cystatin C, eGFR-Cre) Liver function (AST or ALT) 25-hydroxy vitamin D (25OHD) Krebs von den Lungen-6 (KL-6)
Radiological examination	Plain X-ray (Xp) imaging (frontal and lateral chest, both upper and lower limbs, or all frontal images). The modified Sharp score will be calculated every year to assess the progression of joint destruction Bone density (DXA method, lumbar spine, or mean value for both sites)
Comorbidity	Malignant tumor (solid cancer, hematological cancer, among others, the presence or absence of metastasis) Lung disease (IP, COPD, pulmonary tuberculosis, atypical mycobacteriosis, bronchiectasis, or bronchiolitis, among others) Heart disease (myocardial infarction, other cardiovascular disease, chronic heart failure, or peripheral vascular disease, among others) Stroke Hemiplegia or paraplegia Hypertension Diabetes mellitus Hyperlipidemia (hypo-HDL-emia (< 40 mg/dl), hyper-LDL-emia (≥ 140 mg/dl), hypertriglyceridemia (≥ 150 mg/dl) Fracture (spine or femur, among others) Depression Gastrointestinal disease (peptic ulcer or colonic diverticulitis) Liver disease (hepatitis B, hepatitis C, or liver cirrhosis, among other liver dysfunctions) Renal disease (dialysis, decreased renal function [eGFR < 60]) Osteoarthritis (DIP, shoulder, elbow, knee, or hip joints) Herpes zoster Venous thromboembolism (pulmonary thromboembolism or deep vein thrombosis)
Lifestyle and health behavior	Smoking status Physical disability certification and the grade Certification of long-term care needs and the care level Social participation status Exercise habits
Physical examination	Height and body weight Grip strength Body composition (only at institutions where it is possible) Walk speed (only at institutions where it is possible, 10 m at comfortable walking speed) The five-times sit-to-stand test (only at institutions where it is possible)

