### Statistical methods

As registry implementation status, numbers of enrolled individuals, of patients whose data are obtained at each survey period, and of patients who have discontinued will be shown.

For variables related to patient background and treatment status, distribution will be shown by mean with standard deviation, median with IQR, or number and proportion in contingency tables.

The information of serious AEs and person-year will be obtained, and the survival rate with the 95% confidence intervals by treatment options will be estimated by person-year method. Serious AE requiring hospitalization, infectious AE, AE leading to death will be analyzed separately. Impact of baseline variables on each outcome will be investigated using multivariable analysis. A two-tailed *p* < 0.05 will be considered statistically significant. In addition, comparison between the age groups < 75 years old and ≥ 75 years old will be performed.

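### Sustained remission rests on DAS28 < 2.6 alone, with the version unnamed, so it can differ by drug class without a difference in joint status; add a CDAI companion outcome

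*Protocol article*

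**What the plan says.** All places are in the protocol article.

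- **Outcomes.** "Secondary outcomes include the treatment effectiveness and drug retention rates of the initial DMARD". Under effectiveness the article lists sustained remission, low disease activity, and clinically important change in HAQ and EQ-5D. Remission has one definition: "Sustained remission is defined as a Disease Activity Score in 28 joints (DAS28) of < 2.6 for 6 months", extended to 24 and 36 months for the long-term form. No DAS28 version is named and no second criterion is given. The primary outcomes are safety and quality of life.
- **Participants.** Entry is by a first csDMARD, a first MTX course, or the third route: "First b/tsDMARDs treatment is initiated during the study period". The Background notes that "five types of Janus kinase (JAK) inhibitors have been approved".
- **Data collection and management, Table 1.** Laboratory data include "Inflammation marker (CRP, MMP3, ESR" and the symptom items include "Physician global assessment (VAS) Patient global assessment (VAS", together with 28-joint tender and swollen counts.
- **Abstract, Methods/design.** "The factors associated with adverse events and achieving remission will be determined".
- **Statistical methods.** Baseline variables enter a multivariable analysis of each outcome at a two-sided 0.05 level, and a "comparison between the age groups < 75 years old and ≥ 75 years old will be performed". The outcomes compared by age are not named.

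**The concern.** DAS28 adds a logarithmic acute-phase term to the joint counts and the patient's global score. If a drug lowers ESR or CRP directly, beyond what it does to the joints, a patient on that drug can fall below 2.6 with the same joints as a patient on another drug. The cohort mixes drug classes, so drug class could emerge as a factor for remission partly through the formula.

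Adjusting for baseline variables does not help, because the distortion enters the outcome after treatment has started. The results are meant to feed a Delphi consensus on treatment strategies and the JCR guideline revision (Consensus building; Dissemination policy). The Discussion expects them to clarify when b/tsDMARDs are appropriate.

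The unnamed version adds a second problem: ESR and CRP can classify the same patient differently.

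**Working it through.** The article states no figure on this point, so there is none to reproduce. The check is a sensitivity calculation.

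**Assumptions not in the documents**
- DAS28-ESR = 0.56√TJC + 0.28√SJC + 0.70 ln(ESR) + 0.014 GH.
- DAS28-CRP = 0.56√TJC + 0.28√SJC + 0.36 ln(CRP + 1) + 0.014 GH + 0.96.
- CDAI = TJC + SJC + patient global + physician global (globals in cm), with remission ≤ 2.8 and low disease activity ≤ 10.
- Direct drug effects on ESR or CRP, and the ESR ratio across age 75, are given as ranges.

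**1. Same joints, different acute-phase value** (TJC = SJC = 1, GH = 20 mm). The part without ESR is 0.56 + 0.28 + 0.28 = 1.12.
- ESR 20: 1.12 + 0.70 ln 20 = 3.22. ESR 10: 2.73. ESR 5: 2.25.
- The cut-off is crossed at ESR = exp[(2.6 − 1.12)/0.70] = 8.3.
- DAS28-CRP is 2.94 at CRP 10 mg/L and 2.15 at CRP 0.2 mg/L.

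**2. Two patients near the cut-off**

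| | TJC | SJC | ESR | GH (mm) | Physician global (mm) | DAS28-ESR | CDAI |
|---|---|---|---|---|---|---|---|
| A | 3 | 4 | 3 | 20 | 20 | 2.58 (remission) | 3 + 4 + 2 + 2 = 11 |
| B | 0 | 0 | 30 | 20 | 5 | 2.66 (not remission) | 0 + 0 + 2 + 0.5 = 2.5 (remission) |

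By DAS28-CRP, A scores at least 0.97 + 0.56 + 0.28 + 0.96 = 2.77 even at CRP 0, so A is not in remission. B has 0.28 + 0.96 = 1.24 before the CRP term and stays in remission up to CRP = exp(1.36/0.36) − 1, about 42 mg/L. Below that CRP, both patients change status with the version used.

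**3. Size of a drug-class shift**
- Direct 2-fold ESR fall: 0.70 ln 2 = 0.49. Direct 4-fold fall: 0.70 ln 4 = 0.97.
- CRP from 3 to 0.3 mg/L: 0.36 ln(4/1.3) = 0.40. CRP from 10 to 0.5 mg/L: 0.36 ln(11/1.5) = 0.72.
- If DAS28 is normal with mean 2.6 to 3.0 and SD 1.0 to 1.3, a shift of 0.5 adds 15 to 20 percentage points of remission at one visit, and a shift of 1.0 adds 28 to 38.
- With 600 to 700 patients (the recruitment forecast in Sample size), power to declare 38% against 53% different is 96–98% with equal groups, and 84–89% if one group holds 20%.

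**4. Size of the age shift**
- For an assumed ESR ratio of 1.10 to 1.25 between patients aged ≥ 75 and < 75: 0.70 ln 1.10 = 0.07 and 0.70 ln 1.25 = 0.16.
- Under the same distributions this is about 2 to 6 percentage points.
- With equal groups, power to detect 38% against 41% is 11–13%, and 40% against 45% is 24–27%.

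**5. With CDAI.** There is no acute-phase term, so the shift from this source is zero by construction.

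**The case against.** The strongest reply is that the mechanism is not in the documents. They give no DAS28 formula and do not say that any drug lowers ESR or CRP directly or that ESR rises with age. That is correct, and it is why these enter only as assumptions with ranges.

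Several other objections also stand:
- A reader might infer that remission **will** differ by drug and by age. The documents do not support that; what follows is that it can.
- A tenfold ESR contrast (3 against 30) moves DAS28 by 0.70 ln 10 = 1.61, and a reader might take this as the age effect. It is not: the planned contrast lies within a cohort with onset at 65 or older, and the shift in step 4 is far smaller. It also depends on ESR being the version used.
- Patients A and B lie close to the cut-off. Two mm more on A's global (+0.028), or 5 mm less on B's (−0.07), reverses the result. They show the mechanism, not how often it occurs. The percentages in step 3 are for one visit, not for sustained remission.
- No drug-by-drug remission comparison is written. The Discussion compares patient characteristics and adverse events by treatment, and Statistical methods gives survival by treatment option. A remission contrast is only implied by the effectiveness outcome and the promised factor analysis.
- Remission is secondary, and disease activity, joint destruction and patient-reported outcomes are examined separately.
- An article may leave the choice of ESR or CRP to the full protocol. That weakens the complaint about the version, but not the one about a sole criterion, which the article does state.

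Replacing DAS28 outright would not be a clear gain. A patient global of 30 mm adds 0.42 towards 2.6 in DAS28, but 3.0 in CDAI, which exceeds 2.8 with no active joint. In an older cohort with comorbidity, that dependence may bring its own distortion.

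**Conclusion.** The point holds as a cheap improvement to a secondary outcome. DAS28 < 2.6 is the only remission criterion stated, and its version is unnamed. Under the standard formula and an assumed direct 2- to 4-fold ESR fall on some b/tsDMARDs, DAS28-ESR moves by about 0.5 to 1.0 without any change in the joints. A shift of that size is large enough to be declared significant at the forecast enrolment and reported as a treatment factor. If CRP is the version used, the assumed falls give 0.4 to 0.7.

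The age part is minor, at 0.07 to 0.16 units. The documents support neither a claim that results by drug or age are certain to be distorted nor a claim that DAS28 should be dropped. No data are lost, because the components of a criterion without an acute-phase term are in Table 1.

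**What to change.** 1. Keep DAS28 < 2.6 and name one version, ESR or CRP, for all centres and visits.
2. Pre-specify sustained remission and low disease activity by CDAI (≤ 2.8 and ≤ 10, standard cut-offs taken as an assumption) as a companion outcome over the same periods, derived from the 28-joint counts and the two global scores.
3. Report any factor analysis or contrast of remission that involves drug class or age on both definitions. Claim a drug-class association only if it also appears on CDAI.

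The cost is one more derived outcome and a few lines of text, with no new items. One thing to confirm is timing: questionnaires are scheduled only at baseline and Months 12, 24 and 36, and Table 1 does not say at which visits the global scores are taken. Both are needed at each clinical visit used for CDAI, and the patient's score is needed for DAS28 as well. The downsides are a probably lower remission proportion by CDAI and its heavier dependence on the global scores, which should be stated beside the results.

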### Participant timeline

Enrollment was started January 10, 2022, and will be closed on December 31, 2023. Patients will be followed for at least three years after enrollment.

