### Sample size

Given that the LORIS Study is a longitudinal observational study to describe the treatment patterns of LORA, the targeted sample size was not determined. A larger sample size increases the data confidence. According to the past record of each institution, it is expected that approximately 600–700 patients will be recruited.

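### Long-term sustained remission, read as a duration, does not fit the visit schedule: the 36-month limb can be met only by patients already below DAS28 2.6 at baseline

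*Protocol article*

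**What the plan says.** All places are in the protocol article, Methods/design.

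- **Outcomes.** The proportion achieving sustained remission is a secondary outcome. The threshold is given as "Sustained remission is defined as a Disease Activity Score in 28 joints (DAS28) of < 2.6", and the required times as "for 6 months (short-term sustained remission) or for 24, and 36 months (long-term sustained remission". The section does not say when the clock starts or which visits must be below the threshold.
- **Data collection and management.** "Clinical assessment data will be collected at baseline, Month 3, 6, 12, 18, 24, and 36". No later assessment is listed.
- **Participants.** Entry is tied to starting a drug. The third route reads "First b/tsDMARDs treatment is initiated during the study period", and the csDMARD and MTX routes are framed the same way. No minimum disease activity is required.
- **Participant timeline.** "Patients will be followed for at least three years after enrollment".

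**The concern.** The same preposition governs all three limbs, so 6, 24 and 36 months read as lengths of time in remission. The observation window is itself 36 months long and opens at treatment start. A 36-month stretch therefore has to include the baseline visit, before the new drug can have acted.

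The outcome is meant to describe how many patients reach and hold remission on treatment. Applied literally, the 36-month limb selects patients by their state at entry. Two analysts could also report quite different proportions from the same data: one taking the text literally, the other counting remission held from some later visit up to Month 36. The Limitations section says the registry should help in setting target values for RA treatment, so a figure whose meaning turns on the reading could mislead later users.

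**Working it through.** The plan states no figure for this outcome, so there is nothing to reproduce. The check sets the definition against the schedule.

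**Inputs**
- Visits, in months: 0, 3, 6, 12, 18, 24, 36 (Data collection and management).
- Required durations L: 6, 24 and 36 months (Outcomes).
- Month 0 is treatment start (Participants). I take the baseline DAS28 to be measured before the started drug can act.

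**Rule applied.** A patient meets duration L if DAS28 is below 2.6 at every scheduled visit from some visit a to some visit b, with b − a ≥ L.

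**Step 1: spans available**

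| L | Spans of at least L, any start | Spans starting after baseline |
|---|---|---|
| 36 | 0–36 | none; the longest is 36 − 3 = 33 months |
| 24 | 0–24, 0–36, 3–36, 6–36, 12–36 | 3–36, 6–36, 12–36 |
| 6 | many | many; the shortest are 6–12, 12–18 and 18–24 |

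**Step 2: patients not in remission at baseline.** Each of the six later visits is either below 2.6 or not, giving 2^6 = 64 possible patterns. These are counts of patterns, not probabilities.

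- *36 months:* 0 of 64 qualify.
- *24 months:* all three post-baseline spans contain Months 12 to 36. Months 12, 18, 24 and 36 must therefore all be below 2.6, while Months 3 and 6 are free: 2^2 = 4 of 64. Remission may begin earlier than Month 12, but every route includes that stretch.
- *6 months:* two neighbouring visits among Months 6, 12, 18, 24 and 36 must both be below 2.6. Of the 2^5 = 32 patterns on those five visits, 13 have no two neighbours in remission, leaving 19. Month 3 is free: 19 × 2 = 38 of 64.

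**Step 3: size of the effect on the 36-month proportion.** Let p0 be the share with DAS28 below 2.6 at baseline. Only those patients can qualify, so the reported proportion is at most p0. The document gives no p0. With the 600 to 700 patients expected (Sample size), each percentage point of p0 allows at most 0.01 × 600 = 6 to 0.01 × 700 = 7 qualifying patients. The ceiling can lie anywhere from zero upward, depending on p0.

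**The case against.** **The authors may have meant something else.** Since 6, 24 and 36 are all scheduled visits, the phrase could mean remission maintained up to the Month 24 or Month 36 visit, and a condensed article may leave the start point and qualifying visits to the full protocol. This reading is plausible, and it is why the remedy is clarification rather than redesign. It does not dispose of the point. The printed text gives a duration, and that stated duration does not fit the stated schedule, which is more than missing detail.

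**The limb is not logically impossible.** No minimum disease activity is set, and the MTX and b/tsDMARD routes can admit patients already on another csDMARD. Some may start below 2.6 and stay there. This stands, but their result would not show remission achieved on the started drug.

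**Follow-up may exceed three years.** It may, but no assessment after Month 36 is scheduled.

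Three stronger readings are tempting, and the document does not support them:

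- *That the 36-month proportion will be close to zero.* This needs the baseline DAS28 distribution, which is not given.
- *That a misleading 36-month figure will enter the planned consensus and guideline.* Enrolment opened in January 2022, so the first Month 36 visit falls in January 2025. The panel meeting is planned for March 2024 and the guideline revision for 2024. Only later use could be affected.
- *That DAS28 cannot be computed at Months 3, 6 and 18 because patient-reported items are annual.* The text does say "Questionnaires and interview surveys will be conducted at baseline, Month 12, 24, and 36". But Table 1 lists the patient global VAS among symptoms, beside the joint counts and physician global, and assigns no item to particular visits. This needs confirming but is not shown to be a fault.

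**Conclusion.** The point holds for the long-term limbs as worded. Without remission at baseline, the 36-month limb cannot be met (0 of 64 visit patterns), and the 24-month limb requires remission at Months 12, 18, 24 and 36 (4 of 64). The 36-month proportion is capped by the share in remission at entry and so depends on baseline disease activity rather than measuring remission achieved on the started drug.

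This rests on three assumptions: the limbs are durations, baseline precedes any effect of the started drug, and remission is judged at scheduled visits only.

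A reader might infer that the whole remission analysis fails. It does not. The 6-month limb is attainable (38 of 64 patterns), and the abstract's aim of finding factors associated with achieving remission is not tied to the 36-month limb. Severity is moderate: this is part of a secondary outcome, and no primary outcome depends on it.

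**What to change.** Define sustained remission by scheduled visits with a named post-baseline start, before the data are analysed:

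- *Long-term:* DAS28 below 2.6 at every scheduled visit from one named start visit (for example Month 6 or Month 12) through Month 24, and separately through Month 36. Replace the 36-month duration with wording that says through Month 36.
- *Short-term:* DAS28 below 2.6 at two consecutive post-baseline visits 6 months apart, that is Months 6 and 12, 12 and 18, or 18 and 24.
- Confirm that every DAS28 component is recorded at each visit the definition uses.

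The cost is a few sentences and no new visits. The downside is that the labels shrink. Remission through Month 36 then covers 36 − 12 = 24 or 36 − 6 = 30 months, and remission through Month 24 covers 24 − 12 = 12 or 24 − 6 = 18 months; reports should say so. Two limits remain under any such rule. Nothing is assessed between Months 24 and 36, and a patient whose remission begins after the named start visit does not count as long-term.
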